### Exclusion criteria

- Pregnant women will not receive primaquine (urine pregnancy tests will be performed on women of appropriate age groups before drug administration at each TCE round)
- History of allergy or known contraindication to artemisinins, piperaquine or PQ
- Those who are, in the opinion of the study clinician, ill at the time of drug administration

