## Evaluation of participants’ perception, tolerability, safety and acceptability of TCE

The drugs used have been registered or evaluated extensively for malaria treatment but not as much as part of TCE. During the month 3 and the month 12 surveys a questionnaire will be administered to participants or their caregivers to evaluate perception, acceptability, tolerability and safety. Acceptability will be assessed both in terms of drugs received and possible side-effects as well as surveys requiring blood samples. Questions will specifically address whether individuals who refuse to participate or withdraw within the first three months because of unwillingness to give blood samples for the surveys would have joined the study (or not withdrawn) if it had involved receiving TCE without the need to give blood. Focus group discussions (FGDs) as well as in-depth interviews (IDIs) will be conducted to evaluate acceptability. IDIs will include the village leader as well as representative men, women and care givers per village. FGDs and IDIs will be moderated by trained staff based at the village.

The drugs used have been registered or evaluated extensively for malaria treatment but not as much as part of TCE. The months 3 and month 12 surveys questionnaires administered to participants or their caregivers will evaluate safety and will document adverse events (AEs). In this study, an AE is either a drug-related side effect or a new or exacerbation of a pre-existing symptom, sign or illness (other than malaria). A serious AE is one that results in death or is life-threatening, requires inpatient hospitalisation or prolongation of existing hospitalization. All SAEs must be reported by the site investigator to the Medical Monitor or his designee, within one day of his or her awareness of the SAE, who will then report to the study Data Safety Monitoring Board (DSMB). The site investigator must also report the SAEs to the local ethics committee in accordance with local requirements.

In a subsample of up to 10% of the study population a electrocardiogram will be obtained before and after the drug administration to document the safety of the study medication.

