# VI. QUALITY CONTROL AND ASSURANCE PROCEDURES

The study will be conducted in accordance with the current approved protocol, ICH GCP, any national regulations that may apply to this study and SOPs. The MORU Clinical Trials Support Group (CTSG) will monitor adherence to SOPs for collection of clinical data and laboratory specimens and will perform quality checks (curation) of clinical and laboratory data according to standard methodologies. Malaria slide QC will be performed by MORU. Study sites may have in place a system for internal monitoring. In addition, regular external monitoring of all sites will be performed by the MORU CTSG according to a Monitoring Plan. Data will be evaluated for compliance with the protocol and accuracy in relation to source documents. The study drugs comply with regulatory requirements. The quality of study drugs will furthermore be assured by pharmacologic testing of a sample of study drugs in each site.

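### The closed definition of a serious adverse event omits lasting disability, birth defect and other medically important events, so some of these fall outside one-day reporting and the only stated route to the DSMB

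*Protocol*

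**What the plan says.** Protocol section V.5 (evaluation of perception, tolerability, safety and acceptability) first defines an adverse event: "In this study, an AE is either a drug-related side effect or a new or exacerbation of a pre-existing symptom, sign or illness", malaria itself excepted. It then defines seriousness: "A serious AE is one that results in death or is life-threatening, requires inpatient hospitalisation or prolongation of existing hospitalization". No other definition of seriousness appears in the protocol.

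The reporting duty follows directly: "All SAEs must be reported by the site investigator to the Medical Monitor or his designee, within one day" of becoming aware of the event. The Medical Monitor passes the report to the DSMB, and the site also informs the local ethics committee as local rules require. Adverse events in general are recorded by questionnaire at months 3 and 12. No path from those questionnaires to the DSMB is described.

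On pregnancy, the list of exclusion criteria in section V.4.2 says: "Pregnant women will not receive primaquine". It requires a urine pregnancy test before each round. Section V.4 gives DP to every consenting participant in the villages assigned to targeted chemo-elimination (TCE), in three monthly rounds, and says that participants must meet the inclusion and exclusion criteria.

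Section VI adds a general commitment: "The study will be conducted in accordance with the current approved protocol, ICH GCP", together with national regulations and SOPs.

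**The concern.** The definition of seriousness decides which events a site must send on within a day and which the DSMB is bound to see. Here it is a finite list of outcomes with no residual clause. A participant left with a lasting impairment, or an infant born with an anomaly, need not have died, been in danger of death or been admitted to hospital. On the text as it stands such an event is not serious, and no expedited report is due.

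This is a rule that the protocol fixes, not a detail left for a statistical analysis plan. It bears on participant protection in a trial that names safety in its primary objective (section II), and whose own section V.5 says the drugs are less well studied in this use than in malaria treatment. Omitting disability affects every participant. Omitting birth defects bears on any woman who receives DP while pregnant, and the eligibility text appears to allow that.

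**Working it through.** The plan gives no figure on this point to reproduce. The check is a reading of the sections against each other, followed by a rough count.

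**Which events reach the DSMB**

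1. Seriousness criteria in section V.5: death; threat to life; inpatient admission; prolonged admission. There is no wording such as *for example* and no clause for events judged medically important.
2. Trigger for the one-day report: an event that meets criterion 1.
3. Stated route to the DSMB: through the report in step 2, and no other.
4. An event that causes lasting disability, or a birth defect, *and* meets one of the four criteria is reported. One that meets none of them is not covered.
5. For offspring there is a further gap. The adverse event definition speaks of a side effect, symptom, sign or illness and does not mention a participant's child. The protocol describes no follow-up of pregnancies or births. A newborn's anomaly might therefore not count even as a non-serious adverse event.

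**Whether pregnant women can receive DP**

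1. Section V.4.1 admits on age and consent alone.
2. Section V.4 gives DP to all consenting participants in TCE villages, subject to the exclusion criteria.
3. The pregnancy item in section V.4.2 stands among the exclusions, but its only stated consequence is that primaquine is withheld.
4. The more natural reading is that a woman with a positive test stays in and receives DP, in up to three rounds. No sentence says so outright, and the heading over the item points the other way.

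**Rough count of possibly exposed pregnancies per site**

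Inputs: two TCE villages per site and about 250–1200 people per village (section IV.3). Assumptions not in the documents: 2–3% of residents are pregnant during dosing, and everyone takes part.

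- Residents: 2 × 250 = 500 to 2 × 1200 = 2400.
- Lower end: 500 × 0.02 = 10.
- Upper end: 2400 × 0.03 = 72.

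The result is about 10–72 possibly exposed pregnancies per site. Refusals and absences would lower it.

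**The case against.** Four points can be made on the other side.

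*General clauses cover it.* Section VI binds the study to ICH GCP, national rules and SOPs, and ethics committees receive reports under local requirements. A site might therefore report more than section V.5 demands. This stands in part. But a general compliance clause does not clearly override an explicit definition, and the same section has data checked for compliance with the protocol. A site that applied section V.5 literally would be compliant. The documents do not reproduce any external list of seriousness criteria, so this point does not rest on one.

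*Many such events are already serious.* This is correct. Disabling events and anomalies that bring death, danger to life or hospital care are covered, and only the remainder falls through.

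*The number of events is small.* As an illustration only, an assumed anomaly rate of 1–5% would give 10 × 0.01 = 0.1 to 72 × 0.05 = 3.6 anomalies per site, before removing those already serious. The objection stands as to size. It does not remove the case for completing the list.

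*The safety conclusion does not depend on this definition.* A reader might infer that the trial could declare TCE safe without having counted these events. The documents do not support that. Section III.2 takes the safety endpoint from questionnaires, and section V.5 records adverse events through them. A lasting disability from a new illness fits the adverse event definition and can be recorded there. What it lacks is the expedited route. Whether a newborn's anomaly would be captured depends on the scope of the adverse event definition and on birth follow-up, not on the seriousness list.

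**Conclusion.** The point holds in a limited form. The seriousness list in section V.5 is closed and leaves out persistent or significant disability, congenital anomaly or birth defect, and other medically important events. Such an event that meets none of the four listed criteria falls outside the one-day report and outside the only stated route to the DSMB. This follows from the text and needs no numerical assumption.

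The pregnancy aspect adds weight but is an inference from sections V.4 and V.4.2 together. It would be too strong to say that the protocol states that pregnant women are dosed. The passages need to be reconciled, and this review takes no position on who should receive DP. Nor should 10–72 per site be read as a number of unreported events: it is a count of possibly exposed pregnancies under an assumed pregnancy share and full participation.

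The primary endpoint, the sample size and the planned analysis are unaffected. The weakness lies in safety reporting, where correction is cheap and worth making.

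**What to change.** Make three changes to the protocol, and carry the first two into the adverse event form:

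1. In section V.5, extend the seriousness criteria to persistent or significant disability or incapacity, congenital anomaly or birth defect, and other events judged medically important. Apply the existing one-day rule and DSMB route to all of them.
2. In the same section, word the adverse event definition so that an outcome in the offspring of an exposed participant counts once the investigator becomes aware of it. Without this, the added birth-defect criterion could have nothing to attach to.
3. Reconcile sections V.4 and V.4.2 so that the intended handling of DP in women with a positive pregnancy test is explicit, whichever way it is meant.

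The cost is a few sentences, a revised form, brief retraining of sites and a few more expedited reports. These changes create a duty to report events that come to the investigator's notice. They do not by themselves ensure that births are followed up, and should not be presented as doing so.

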# VI. QUALITY CONTROL AND ASSURANCE PROCEDURES

The study will be conducted in accordance with the current approved protocol, ICH GCP, any national regulations that may apply to this study and SOPs. The MORU Clinical Trials Support Group (CTSG) will monitor adherence to SOPs for collection of clinical data and laboratory specimens and will perform quality checks (curation) of clinical and laboratory data according to standard methodologies. Malaria slide QC will be performed by MORU. Study sites may have in place a system for internal monitoring. In addition, regular external monitoring of all sites will be performed by the MORU CTSG according to a Monitoring Plan. Data will be evaluated for compliance with the protocol and accuracy in relation to source documents. The study drugs comply with regulatory requirements. The quality of study drugs will furthermore be assured by pharmacologic testing of a sample of study drugs in each site.

# VII. ETHICS

The Investigators will ensure that this study is conducted in compliance with the current revision of the Declaration of Helsinki 2013 and according to any National Regulations. The study protocol and its associated documents will be submitted to the Oxford Tropical Research Ethics Committee (OXTREC) and the appropriate local ethics committees for written approval. The Investigator will submit and, where necessary, obtain approval from the above parties for all substantial amendments to the original approved documents.

This study will use drugs that have been studied thoroughly and their toxicities are well described. In general, they are all well tolerated. The main reported effects for DP are gastrointestinal upset (nausea, vomiting, abdominal pain and diarrhoea) as well as dizziness, headache and disturbed sleep. Rates of these side effects are generally < 10% and often <5% except for dizziness (~12%) [11]. The main adverse effects for PQ are also gastrointestinal, and haemolytic episodes reported in G6PD deficient individuals. These effects however are not expected in this study, as the dose of PQ used will be lower (0.25 mg/kg) than the currently used (0.75 mg/kg) when administered as single dose for falciparum malaria treatment. Based on a PQ safety review recently conducted by MORU, the WHO MPAC modified its recommendation for PQ single dose falciparum treatment changing it from 0.75 mg/kg to 0.25 mg/kg in areas where the prevalence of G6PD deficiency is considered high enough to impose a risk to this population when G6PD testing is not available; this change eliminates the need for G6PD testing [10]. Primaquine will not be used in Cambodia as it is not in the local treatment guidelines.

# VIII. DATA HANDLING, ACCESS AND PUBLICATIONS

Direct access will be granted to authorised representatives from the sponsor and host institution and the regulatory authorities, if applicable, to permit trial-related monitoring and inspections. All study data will be recorded on standard Case Report Forms (CRF) and entered into a secure database. The participants will be identified by a study-specific participant number and/or code in any database. The name and any other identifying detail will NOT be included in any study data electronic file. Data may be used alone or in combination with data from related studies in secondary analyses. Any data published in the peer-reviewed medical literature will protect the identity of the subjects. All those who have made a substantial contribution will be coauthors on publications which will be open access. The sites have the right to publish their data individually and to include members of the sponsor’s team who have made a significant contribution. There will also be publications of pooled data which will be coordinated by the MORU group. All sites will have the opportunity to contribute to these publications.

